## Feasibility Assessment

The feasibility of the study will be assessed by NIAID the sponsor within 12 months of enrolling the initial participant. If less than 90% of the study sample (with day 14 confirmation of eligibility) has been enrolled, the study sponsor will consider terminating the study enrollment and/or follow-up.

## Population for Analysis

All participants enrolled in the study will be analyzed. Any control participants who later becomes infected with measles or participants from either group that become pregnant will be censored at the time of infection or pregnancy.

If a participant who was enrolled as a case is later diagnosed with measles during the study, there is no change with regards to how their data will be analyzed or with regards to other study procedures. However, as a measles infection should confer lifelong immunity, this scenario is expected to be extremely unlikely.

A participant who has received rabies PEP during the study prior to the timepoint at which they were scheduled (randomized) to receive rabies vaccination will be excluded from the primary analysis of the rabies vaccine but included in the immune amnesia analysis.

Participants who have received their first dose of rabies PrEP as scheduled (randomized) will be analyzed as planned.

Participants who do not receive a full course of rabies vaccine will be included in all analyses. A sensitivity analysis will be performed where these participants are excluded.

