## Schedule of Activities

Table 1. Schedule of study evaluations and procedures.

|  | **Visit 0** | **Visit 0.1** | **Visit 1** | **Visit 2^a^** | **Visit 3^a^** | **Visit 4^a^** | **Visit 5** | **Visit 6** | **Visit 7** | **Visit 8^b^** | **Visit 9^b^** | **Visit 10^b^** | **Visit 11** |
| --- | --- | --- | --- | --- | --- | --- | --- | --- | --- | --- | --- | --- | --- |
| **Evaluation/**  **Procedure** | **Screening/ Enrollment^c^ Blood Draw** | **Serology repeat (Retest for measles IgM)** | **Randomization**  **Blood Draw** | **Early rabies vaccine Dose 1** | **Early rabies vaccine Dose 2** | **Early rabies vaccine Dose 3** | **Blood draw**  **Healthcare Ques** | **Healthcare Ques** | **Healthcare Ques** | **Late rabies vaccine Dose 1** | **Late rabies vaccine Dose 2** | **Late rabies vaccine Dose 3** | **Blood draw**  **Healthcare Ques** |
| **Timepoint**  **(Window)** | **Day 0^c^** | **Day 7-10^c^** | **Day 14^c^**  **(±2 days)** | **Week 8**  **(±3 days)** | **Week 9**  **(+2 days)** | **Week 11-12** | **Week 13**  **(+3 days)** | **Week 26**  **(±2 weeks)** | **Week 39**  **(±2 weeks)** | **Week 47**  **(±3 days)** | **Week 48**  **(+2 days)** | **Week 50-51** | **Week 52**  **(+3 days)** |
| Informed consent/assent | X |  |  |  |  |  |  |  |  |  |  |  |  |
| Inclusion/ Exclusion^c^ | X | | |  |  |  |  |  |  |  |  |  |  |
| Vital signs^d^ | X |  | X | X^d^ | X^d^ | X^d^ | X | X | X | X^d^ | X^d^ | X^d^ | X |
| MUAC^e^, height, weight | X |  |  |  |  |  |  |  |  |  |  |  | X |
| Demographics | X |  |  |  |  |  |  |  |  |  |  |  |  |
| Upper respiratory specimen (OP/NP swab) for measles PCR | X |  |  |  |  |  |  |  |  |  |  |  |  |
| HIV^f^ | X^g^ |  |  |  |  |  |  |  |  |  |  |  | X^f^ |
| Hemoglobin level^h^ | X |  | X |  |  |  | X |  |  |  |  |  | X |
| Urine pregnancy test^h^ | X^i^ |  | X | X^i^ | X^i^ | X^i^ | X |  |  | X^i^ | X^i^ | X^i^ | X |
| Measles IgM/IgG | X^g^ | X |  |  |  |  |  |  |  |  |  |  |  |
| Medical history | X |  |  |  |  |  | X |  |  |  |  |  | X |
| Concomitant medications | X |  | X | X | X | X | X | X | X | X | X | X | X |
| Physical examination | X |  | X |  |  |  | X | X | X | X |  |  | X |
| Optional photography (skin rash and Koplik spots)^j^ | X |  |  |  |  |  |  |  |  |  |  |  |  |
| Randomization to early or late rabies vaccine |  |  | X |  |  |  |  |  |  |  |  |  |  |
| Measles vaccine^k^ |  |  | X |  |  |  |  |  |  |  |  |  |  |
| AE assessment |  |  | X | X | X | X | X | X | X | X | X | X | X |

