| Healthcare Utilization Questionnaire |  |  |  |  |  |  | X | X | X |  |  |  | X |
| Rabies vaccine |  |  |  | (X) | (X) | (X) |  |  |  | (X) | (X) | (X) |  |
| Research blood collection^l^ | X |  | X |  |  |  | X |  |  |  |  |  | X |
| Vitamin A | X^m^ |  |  |  |  |  |  |  |  |  |  |  |  |

Abbreviations: AE, adverse event; HIV, human immunodeficiency virus; Ig, immunoglobulin; MUAC, mid-upper arm circumference; NP, nasopharyngeal; OP, oropharyngeal; PCR, polymerase chain reaction.

(X) = Each participant will receive only one 3-dose series of rabies vaccine according to randomization to early group (vaccination at Visits 2, 3, and 4) or late group (vaccination at Visits 8, 9, and 10).

^a^ EARLY rabies vaccination: Only participants randomized to EARLY rabies vaccine attend Visits 2, 3, 4. Visit 2 occurs 8 weeks after Day 0; Visit 3 occurs 7 days after Visit 2; Visit 4 occurs 21 to 28 days after Visit 2 AND at least 14 days after Visit 3.

^b^ LATE rabies vaccination: Only participants randomized to LATE rabies vaccine attend Visits 8, 9, 10. Visit 8 occurs 47 weeks after Day 0; Visit 9 occurs 7 days after Visit 8; Visit 10 occurs 21 to 28 days after Visit 8 AND at least 14 days after Visit 9.

^c^ Day 0 is defined as the day screening occurs and the first research blood sample is collected. Inclusion/exclusion criteria evaluation for enrollment will be completed when PCR and measles IgG/IgM and HIV results are available, generally by Day 14. In cases where the clinical presentation is consistent with measles but the Day 0 tests (measles PCR and measles IgM) are negative or equivocal, an optional retest of the measles IgM can be done between Days 7 and 10. The guardian/parent will be informed of the need for a retest and asked to bring the child back to the clinic. Blood will be collected via finger stick for the retest and results will be available by Day 14. All potential participants (or guardian/parent) will be informed of eligibility status by a designated study staff by phone, if possible, prior to the Day 14 scheduled study visit or at the Day 14 scheduled study visit. Ineligible participants may be invited to the site to discuss test results and referral for measles vaccination if serum IgG and IgM are both negative.

^d^ Vital signs include temperature, heart rate, and respiratory rate; may be obtained prior to rabies vaccine administration, if clinically indicated.

^e^ MUAC in children 12 to 59 months old.

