# STUDY DESIGN

## Overall Design

This is a prospective, observational, longitudinal study to be conducted in select African regions to investigate the effects of MeV infection on pre-existing immunity, immune response to a known controlled immune stimulus (rabies vaccine), and susceptibility to infection to prevalent pathogens. Although children will receive the rabies vaccine as part of this study, we consider this an observational study rather than an interventional study. An interventional study tests an outcome of that intervention, e.g., efficacy or safety. The rabies vaccine is not used as a research intervention in this sense, i.e., we are not testing the efficacy or safety of the rabies vaccine, but rather using the vaccine as an immune stimulus to understand the effect of measles immune amnesia over time. In other words, the rabies vaccine is not the object of this investigation, but merely a means to allow assessment of the research objectives. Other vaccines could be used for this purpose, but rabies vaccine is convenient because there will not be pre-existing immunity to confound the results. The study is expected to take place in a subset of the NIAID Division of Clinical Research (DCR) Special Projects sites and any additional site(s) that may be identified. Specific study sites within each country will be in areas experiencing measles outbreaks.

We will enroll approximately 256 children aged 1-15 years into study Group 1 (acute MeV infection) or Group 2 (no acute measles infection). See section 5.1 for specific group criteria. In each group, approximately half of the enrolled participants will be ages 1-5 years and approximately half will be ages 6-15 years. Group 2 will be matched to Group 1 on gender and catchment area of study implementation.

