Participants will undergo blood collection for screening and research testing at Day 0, between Days 7 and10 (optional, if Day 0 measles PCR and IgM are negative or equivocal in a child that presents with signs and symptoms consistent with measles), Day 14, Week 13, and Week 52. An upper respiratory specimen for MeV PCR will be collected at Day 0. Urine will be collected from females of reproductive potential to check for pregnancy at study visits with rabies vaccination or research blood collection. Hemoglobin levels will be checked at each study visit prior to research blood collection. Research samples will be tested for humoral and cellular immune responses to rabies vaccination (used as a controlled immune system stimulus, see section 8) and other research testing as described below (section 7.3). In addition, targeted sequencing will be performed on the measles virus to identify specific genotype. Unbiased sequencing will be used to try to identify the etiology in participants who have signs and symptoms consistent with measles but who test negative for measles by PCR and IgM. Optional photographs will be taken of the rash and/or Koplik spots at Day 0 to characterize the phenotype of the participants who test positive or negative for measles. We will also collect information on healthcare system encounters throughout the study period to help determine the clinical impact of immune amnesia after measles infection.

Participants with acute measles at screening/enrollment will be provided vitamin A treatment if they have not previously received it as part of their treatment. The treatment will follow WHO guidelines: 2 doses of 200,000 IU to be taken orally, 24 hours apart. The first dose will be given at the screening/enrollment visit, and the second dose will be given to the parent/guardian to be given the following day. A participant who has a rabies exposure during study participation will be provided rabies PEP with HRIG and rabies vaccine according to standard practice and the approved Verorab dosing schedule and depending on PrEP status. Any participant who receives rabies PEP prior to the timepoint that they were scheduled (randomized) to receive rabies PrEP under this study will continue in the study for follow-up visits but not receive PrEP according to their assigned randomization schedule. Data from these participants will be analyzed as described in Section [8.3](#_Population_for_Analysis).

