# STUDY POPULATION

## Inclusion Criteria

To be eligible to participate in this study, an individual must meet all of the following criteria:

1. Aged 1 to 15 years.
2. Ability of the participant’s legal or culturally acceptable representative to provide informed consent.
3. Ability to give assent, as appropriate.
4. Stated willingness of parent/guardian and participant as appropriate, to comply with all study procedures.
5. Willingness to receive rabies vaccine.
6. Meet the criteria for assignment to Group 1 or Group 2, as follows:
   1. Group 1, cases (acute MeV infection):

- Clinical signs and symptoms suggestive of acute MeV infection (Koplik spots or skin rash) AND
- Laboratory confirmed measles:
  - - - - Upper respiratory specimen (swab) PCR for measles positive.

OR

- - - - - Serum IgM for measles positive.
  1. Group 2, controls (no acute MeV infection):
- No clinical signs and symptoms suggestive of acute MeV infection (Koplik spots or skin rash) AND
  - - - Upper respiratory specimen (swab) PCR negative for MeV AND
      - Serum measles IgM negative AND
      - Serum measles IgG positive and previously vaccinated for measles (2^nd^ dose will be offered if appropriate). If serum measles IgG is negative, participant must be willing to be vaccinated regardless of prior measles vaccine history to meet this criterion.

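### No measles test is scheduled for controls after Day 0, so the rule that censors infected controls will miss silent, mild or unreported infections

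*Protocol*

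**What the plan says.** **The rule.** Protocol Section 8.4 singles out "Any control participants who later becomes infected with measles": follow-up of such a child is cut off, for analysis, on the date of infection. Pregnancy in either group is handled the same way. To apply the rule, the team must know that the infection happened and when.

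**The setting.** Section 4.1: "Specific study sites within each country will be in areas experiencing measles outbreaks", and "Group 2 will be matched to Group 1 on gender and catchment area of study implementation". Controls therefore come from the same places as the cases.

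**The tests.** Section 4.1: "An upper respiratory specimen for MeV PCR will be collected at Day 0". Table 1 (Section 1.3) repeats this and marks measles IgM/IgG at Visits 0 and 0.1 only. Footnote c limits the Visit 0.1 retest: "In cases where the clinical presentation is consistent with measles but the Day 0 tests (measles PCR and measles IgM) are negative or equivocal". Section 5.1 requires controls to be free of Koplik spots and rash, so that retest is not for them.

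**Who can be a control.** Section 5.1 admits children who are IgG positive and already vaccinated. It also admits IgG-negative children: "If serum measles IgG is negative, participant must be willing to be vaccinated regardless of prior measles vaccine history to meet this criterion". Table 1 places their vaccination at Visit 1 (Day 14), given by the study or by referral.

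**The concern.** A control is classified once, on Day 0, by absence of signs, a negative PCR and a negative IgM. A child exposed shortly before Day 0 can meet all three conditions while incubating. An IgG-negative child stays susceptible at least until the Day 14 vaccine takes effect, and longer if vaccination is by referral. No later measles test would reveal either infection.

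An infected control who is not recognised brings the exposure under study into the comparison group. If measles has the effect the trial is looking for, the antibody panel, rabies titer and healthcare encounter contrasts all shrink. Nothing in the scheduled data would show that this had happened, or show that it had not.

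**Working it through.** **1. How a control's later infection could come to light**

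| Route | Where | What it offers |
|---|---|---|
| Measles PCR | Table 1; Section 4.1 | Day 0 only |
| Measles IgM/IgG | Table 1, footnote c | Day 0; the Day 7-10 retest is for measles-like presentations only |
| Physical examination | Table 1; Section 7.2 | Day 14 and Weeks 13, 26, 39 and 52, plus Week 47 in the late-vaccine group; a check for measles signs is specified only for Visit 0 |
| Medical history | Table 1 | Weeks 13 and 52 |
| Healthcare questionnaire | Table 1; Section 7.2 | Weeks 13, 26, 39 and 52; encounters collected as far as possible |
| Adverse events | Section 7.2 | Events judged unrelated to research procedures are not recorded |
| Site manual | Section 4.1 | Follow-up once infection is suspected |
| Stored plasma | Section 7.3 | Further antibody assays permitted, none required for this purpose |

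Every active route after Day 0 is clinical or depends on a report. An illness with rash that the family mentions, or that leads to a clinic visit, can be found and roughly dated. An infection with little or no rash, or one that begins and ends between examinations unreported, cannot.

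**2. The protocol's own design figures**

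Two-sample t-test with n per group, df = 2n - 2 and noncentrality d × √(n/2):

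- Rabies titer (Table 2): n = 30 per cohort, two-sided alpha 0.05. The difference detectable with 90% power is 0.851; the protocol states 0.85. Power at 0.85 is 89.9%.
- Antibody panel (Table 3): n = 60 per arm within an age group, alpha 0.025/1000 per side. The detectable difference is 1.010; the protocol states 1.00. Power at 1.00 is 89.1%.
- Encounters (Section 8.2): 0.5 versus 0.7. Power is 89.0% with 120 per group and 90.9% with 128; the protocol states 90%.

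The stated figures reproduce closely.

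**3. What missed infections would cost**

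Let c be the share of controls infected **and missed**. The protocol does not give c, so the values below are assumptions. If each missed infection carries the full case effect, the difference becomes d × (1 - c), and the control encounter proportion becomes 0.5 + 0.2c.

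| c | Controls out of 128 | Panel d | Panel power | Rabies d | Rabies power | Encounter power (120 per group) |
|---|---|---|---|---|---|---|
| 0 | 0 | 1.00 | 89.1% | 0.850 | 89.9% | 89.0% |
| 1% | 1.3 | 0.99 | 88.0% | 0.842 | 89.3% | 88.4% |
| 2% | 2.6 | 0.98 | 87.0% | 0.833 | 88.7% | 87.8% |
| 5% | 6.4 | 0.95 | 83.3% | 0.807 | 86.8% | 85.8% |

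Mixing infected and uninfected children also widens the spread in the control group. Allowing for this at c = 5% gives 81.8% for the panel and 86.2% for rabies.

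**4. What c is made of**

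c = (share IgG negative) × (share of those infected) × (share of infections missed)

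None of the three is in the protocol. For illustration, 20-40% IgG negative and 10-25% of those infected gives 0.20 × 0.10 = 2% to 0.40 × 0.25 = 10% of controls infected. If half of these are missed, c is 1-5%. If one in five is missed, c is 0.4-2%.

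**The case against.** The strongest reply is that the risk is already reduced at entry. Controls are either IgG positive and vaccinated, or IgG negative and to be vaccinated. Section 7.2 gives the aim of that vaccination as keeping controls free of natural measles during the study. This stands, and it confines the main exposure to IgG-negative controls in a short window around Days 0 to 14. It does not close that window. The remark in Section 8.4 that later measles is very unlikely concerns cases, not controls.

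A reader might infer that the censoring rule cannot be applied at all. The protocol does not support that. Scheduled examinations, history, the questionnaire and the site process give real opportunities to find overt measles, and the site manuals, which may say more, are not at hand.

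A reader might also infer contamination of up to 10%, with panel power of 76% and rabies power of 83%. That treats every infected control as missed, although Section 8.4 removes those who are noticed. It also gives a mild, unnoticed infection the same effect as a case, whereas Section 5.1 requires cases to have rash or Koplik spots as well as laboratory confirmation. The same full-effect assumption underlies the table above, so its losses lean high for any given c.

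Finally, a serological definition or sensitivity analysis could sit in an SAP, which is not available here. That is fair for the definition. But an SAP cannot use an assay that was never run, nor settle whether blood is drawn before or after the Day 14 vaccine.

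**Conclusion.** The point holds in limited form. Section 8.4 depends on knowing about infections that the visit schedule does not test for. Overt measles in a control can be recognised and censored; silent, mild or unreported infection cannot, and it biases the contrasts toward no difference.

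The size cannot be fixed from the protocol. At 1-2% of controls infected and missed (about 1 to 3 of 128), the loss is about 1 to 2 points of power for the panel and about 1 point for rabies. At 5% (about 6 of 128) it is about 6 and 3 points. These figures assume that each missed infection carries the full case effect. The low end is plausible given the entry and vaccination rules, but without testing the trial could not show it. This is a cheap improvement worth making, not a flaw that undermines the design.

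**What to change.** In Table 1 and Section 8.4:

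1. State that the Day 14 research sample is drawn before any measles vaccine given that day. Table 1 places both at Visit 1 without giving an order.
2. Run measles IgM/IgG on that stored plasma for controls who were IgG negative on Day 0. Treat those who are positive, with no recorded measles vaccination since Day 0, as infected under the existing censoring rule.
3. For controls with no recorded measles vaccination during the study, compare measles IgG in the Day 0, Week 13 and Week 52 plasma, or use measles targets in the multiplex panel if present. Prespecify what counts as a rise, and use it only in a sensitivity analysis that excludes those controls. A rise without illness does not match the case definition, so it should not drive the main analysis. The vaccination condition is needed because Section 5.1 allows a second dose to be offered to some IgG-positive controls.
4. State that infection after the Day 14 draw in newly vaccinated controls cannot be resolved serologically, because a later IgG rise may be the vaccine response, and that it relies on clinical ascertainment.

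The cost is a small number of added assays on plasma already drawn, some protocol wording and a few censored controls. No extra visit or blood draw is needed.

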## Statistical Analyses

### General Approach

Demographic variables will be summarized overall by group and by group and country. Binary endpoints will be reported as proportions with 95% Wilson score confidence intervals (CIs) or logistic regression model coefficients and CIs. Continuous endpoints will be summarized with means and standard deviations and/or geometric means and CIs based on the t-distribution or using regression models. Participants with missing data may be dropped from the analysis.

### Analysis of Primary Endpoints

The analysis of the rabies antibody will be performed using a 0.05 level two-sided test as described in the sample size determination (section 8.2). 95% CIs around the parameter estimates will be provided. The panel of antibodies will be analyzed using t-tests and controlling the 2-sided 0.05 error rate via a Westfall Young approach as this will be more powerful than a Bonferroni correction.

### Analysis of Secondary Endpoints

The proportion of participants hospitalized between groups will be reported, exact conditional tests will be performed, and 95% Wilson score CIs will be calculated. A Poisson analysis will be used to compare the number of encounters with medical providers between groups. The average number of encounters per group per person will be calculated and compared. Since each person will have 1 year of follow-up, this would be appropriate. If participants drop out, we will adjust for time in study for each person.

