# STUDY OBJECTIVES

The objectives for this study are:

| **OBJECTIVES** | **ENDPOINTS** | **JUSTIFICATION FOR ENDPOINTS** |
| --- | --- | --- |
| **Primary** | | |
| To determine if MeV infection induces a loss of pre-existing immunity (immune amnesia) to endemic pathogens at Week 13 after baseline in children in select African regions. | Mean change in a panel of antibody levels over 13 weeks as measured by multiplex serological methods (e.g. PhIP-Seq/VirScan or SeroChip) and targeted ELISAs for confirmation. | These methods detect antibodies against multiple diverse pathogens and epitopes and assess both neutralizing and non-neutralizing antibodies. |
| To determine the effect of MeV infection on immune response to a controlled immune stimulus (rabies vaccination) at early and late timepoints post-infection. | Proportion of subjects with rabies virus neutralizing antibodies (RVNA) titer ≥ 0.5 International Units per milliliter (IU/mL) as measured by rapid fluorescent focus inhibition test 14 days after the last PrEP regimen vaccination. | These tests will measure the immune response and functionality of antibodies raised against the rabies vaccine. |
|  | Proportion of subjects with an RVNA titer ≥ lower limit of quantification 5-6 weeks after the first rabies vaccine dose. |  |
|  | Geometric mean RVNA titer 5-6 weeks after the first rabies vaccine dose. |  |
| **Secondary** | | |
| To determine if there is an increase in healthcare system encounters in the year following enrollment in children with recent MeV infection compared to those without recent MeV infection. | Mean number of non-study sick visit healthcare system encounters during the 1-year follow-up. | Visits to the healthcare system for sick visits in the year following enrollment in children with recent MeV infection will help determine the clinical impact of the immune amnesia in an objective manner. |
| To determine if MeV infection induces a loss of pre-existing immunity (immune amnesia) to endemic pathogens at Week 52 after baseline in children in select African regions. | Mean change in a panel of antibody levels over 52 weeks as measured by multiplex serological methods (e.g., PhIP-Seq/VirScan or SeroChip) and targeted ELISAs for confirmation. | These methods detect antibodies against multiple diverse pathogens and epitopes. These represent the spectrum of both neutralizing and non-neutralizing antibodies. |
| **Exploratory** | | |

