We also present sample size calculations to show detectable change over time between groups in the panel of antibody measurements. This analysis will compare change in the panel of measurements from baseline to the 3-month blood draw between groups. The panel will contain numerous measurements, so we will use a Bonferroni correction to control the study-wide error rate at p=0.05. To be conservative, we will assume 1000 comparisons and plan to maintain the alpha level at a two-sided 0.05 rate (thus the power calculations will be performed with alpha=0.025/1000). We will perform the analysis separately for children aged 1-5 years and those aged 6-15 years. Table 3 gives the detectable between-group standardized difference (difference/std) with 90% power for different samples sizes with the Bonferroni correction for multiple comparisons. Here we combine the early and late rabies randomization groups since the rabies vaccination should not affect the comparison of other antibodies.

Table 3. Detectable standardized differences with 90% power.

The sample size is the number needed in an arm (measles or control), age group (young vs old (multiply by 4 for total sample size)

| Sample size per arm (total study sample size) | Standardized detectable difference |
| --- | --- |
| 40 (160) | 1.26 |
| 60 (240) | 1.00 |
| 80 (320) | 0.86 |

Note: The detectable difference of 1.00 that can be seen with a sample size of 240 is well within what the Mina paper found and is a reasonable sample size for this study.[[12](#_ENREF_12)]

Power for medical visit endpoint.

A particularly important secondary endpoint is healthcare encounters. We have calculated the power to compare health care encounters between the MeV and control groups for the selected sample size. One method to summarize healthcare encounters is to look at the proportion of participants in each group that had at least one medical visit. Using this measure, there would be 90% power to detect a difference in proportions of 0.5 versus 0.7 (control group versus MeV group, respectively) using a test of proportions. Note a proportion of 0.5 for the control group was used since this proportion gives the largest variance. Any larger or smaller proportions will allow smaller difference in proportions to be detected with 90% power. In the analysis, the Poisson test may be used which would be more powerful if participants have multiple healthcare encounters.

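### Section 8.5.3 justifies a Poisson analysis of encounter counts by equal follow-up alone; if sick visits are overdispersed, a model-based Poisson interval is too narrow

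*Protocol*

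**What the plan says.** The secondary endpoint in Protocol section 3 is a count per child: "Mean number of non-study sick visit healthcare system encounters during the 1-year follow-up". Section 8.2 gives it weight: "A particularly important secondary endpoint is healthcare encounters".

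Section 8.5.3 fixes the method: "A Poisson analysis will be used to compare the number of encounters with medical providers between groups". The reason given is "Since each person will have 1 year of follow-up, this would be appropriate". The one adjustment named is for exposure: "If participants drop out, we will adjust for time in study for each person".

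Section 8.2 bases its power statement on a different summary, the proportion of children with at least one visit: "there would be 90% power to detect a difference in proportions of 0.5 versus 0.7". It then adds: "In the analysis, the Poisson test may be used which would be more powerful if participants have multiple healthcare encounters".

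The Protocol nowhere mentions overdispersion, a robust or scaled variance, or a negative binomial model. It states no expected visit rate and no variance.

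**The concern.** A model-based Poisson standard error is right only when the variance of the count equals its mean. Following every child for the same time does not secure this. Children aged 1 to 15, recruited in more than one country, will differ in how often they fall ill and how easily they reach care, and one illness can lead to several visits. Each of these features pushes the between-child variance above the mean. Balance between the groups on age, gender or catchment area does not remove differences between individual children.

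If the variance is larger than the mean and the analysis ignores it, the interval for the rate ratio is too narrow and the null is rejected too often. A false positive here would be read as clinical support for immune amnesia. Section 8.2 also treats repeat visits purely as a gain in power. Without a suitable variance, part of that gain could be understated error.

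**Working it through.** **Inputs from the Protocol.** 128 children per group; 6.5% loss to follow-up, so 256 × (1 − 0.065) = 239.4, or about 120 per group; at-least-one-visit proportions of 0.5 (control) and 0.7 (measles) (all section 8.2).

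**Assumed.** A two-sided 5% level for encounters, since section 8.5.3 states none. A dispersion φ = variance/mean from 1 to 4, since the Protocol gives none.

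**Step 1: the Protocol's own power figure.** Test of two proportions, pooled variance under the null, no continuity correction.

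- 128 per group: null SE = √(2 × 0.6 × 0.4/128) = 0.0612; alternative SE = √((0.25 + 0.21)/128) = 0.0599; z = (0.2 − 1.96 × 0.0612)/0.0599 = 1.33; power 90.9%.
- 120 per group: the same calculation gives 89.0%.

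The stated 90% is reproduced. It belongs to the proportion, not to the Poisson count analysis.

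**Step 2: a model-based Poisson test under overdispersion.** If the variance is φ × mean, the true standard error of the log rate ratio is √φ times the Poisson one. The true type I error is therefore 2 × (1 − Φ(1.96/√φ)), and the interval should be √φ times wider.

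| φ | 1.96/√φ | True type I error | Coverage of the 95% CI | Correct width ÷ Poisson width |
|---|---|---|---|---|
| 1 | 1.96 | 5.0% | 95% | 1.00 |
| 1.25 | 1.75 | 8.0% | 92% | 1.12 |
| 1.4 | 1.66 | 9.8% | 90% | 1.18 |
| 1.5 | 1.60 | 11.0% | 89% | 1.22 |
| 2 | 1.39 | 16.6% | 83% | 1.41 |
| 3 | 1.13 | 25.8% | 74% | 1.73 |
| 4 | 0.98 | 32.7% | 67% | 2.00 |

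**Step 3: simulation check.** Negative binomial counts were simulated with no group difference, at means of 0.69 to 3 visits per child, 120 and 128 per group, 20,000 trials per setting. The Poisson Wald test rejected in 10.6–11.2% of trials at φ = 1.5, 15.6–16.7% at 2, 25.3–26.3% at 3 and 31.8–33.0% at 4. With a robust (sandwich) variance, rejection stayed between 4.9% and 6.2% for φ from 1 to 4.

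**Step 4: power after the correction.** For negative binomial counts, P(no visit) = φ^(−mean/(φ − 1)), so mean = −ln P(no visit) × (φ − 1)/ln φ. With P(no visit) of 0.5 and 0.3, the log rate ratio is ln(1.204/0.693) = 0.552 at every φ. At φ = 2 the means are 1.00 and 1.74. With 120 per group, SE = √(2 × (1/120 + 1/208.4)) = 0.162, and power = Φ(0.552/0.162 − 1.96) = 93%. The same approximation gives 98% at φ = 1, 95% at 1.5, 88% at 3 and 84% at 4. The proportion test has 89.0% at this size.

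**The case against.** The strongest reply is that section 8.5.3 does not name a variance estimator. Poisson regression with a robust variance is still a Poisson analysis, and a statistical analysis plan that is not shown could specify one. This stands to a degree: the inflation above applies to the model-based variance. But the Protocol names the model and defends it with a reason that concerns exposure only, so the text needs correcting whatever a later document adds.

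Four stronger readings are tempting and are not supported:

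- **That the error rate will be well above 5%.** At φ = 1 it is 5%, and the Protocol gives nothing from which φ can be estimated.
- **That the planning value of 0.5 points to overdispersion.** Section 8.2 chose it because it maximizes the variance of a proportion. It fits a Poisson count with mean 0.69 and φ = 1 as well as it fits any overdispersed count.
- **That the Poisson result is the study's only clinical evidence.** Section 8.5.3 also compares hospitalization with exact tests, and section 8.2 powers the at-least-one-visit proportion. Count overdispersion affects neither.
- **That the power remark in section 8.2 is wrong and should go.** Repeat visits are not the same as overdispersion: a Poisson count with mean 3 has many repeat visits and variance equal to its mean. With a robust variance, counts still give 93–98% power at φ from 1 to 2, against 89.0% for the proportion. They fall below it at φ of 3 and 4.

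**Conclusion.** The point holds in conditional form. Equal one-year follow-up does not justify the Poisson variance, and the Protocol makes no provision for overdispersion in a count where it is likely. If the model-based variance is used, even φ = 1.25 raises the type I error to about 8%, and φ = 1.5 roughly doubles it. The size rests on the assumed range of φ and on an assumed two-sided 5% level. The consequence is limited to the count comparison of one secondary endpoint, but the Protocol itself singles that endpoint out. The correction is affordable at the planned size: power stays at 84–98% under the assumptions shown.

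**What to change.** In section 8.5.3, specify Poisson regression with robust (sandwich) or quasi-likelihood variance, or negative binomial regression, with log time in study as offset. Report the rate ratio with its 95% CI. Drop the statement that equal follow-up makes the analysis appropriate, or confine it to the exposure term.

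In section 8.2, keep the remark on the Poisson test's greater power but add that the gain depends on a variance that allows for overdispersion.

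Extra covariates are a separate modelling choice that this defect does not require.

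The cost is a line or two of text and wider intervals when overdispersion is present. When it is absent, almost nothing is lost: at φ = 1 the robust test rejected in 4.9–5.3% of simulated trials.
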